### 2.8 Study interventions

In this study, patients will apply an LP5 or placebo patch for 12 h daily on the day before surgery and on postoperative days 1, 2, and 3. The preoperative patch will cover the anticipated incision site, while the postoperative patches will be applied 1.5 cm from either side of the incision. The placebo group will apply a placebo patch, identical in appearance and packaging to the actual medication patch. The lidocaine patches and placebo patches used in this study will be manufactured by Beijing Tide Pharmaceutical Co., Ltd. To maintain blinding, both patients and researchers will remain unaware of group assignments. The patches will be applied by medical professionals who are not involved in patient recruitment or data collection. Randomization will be performed before the study begins by an independent researcher using a computer-generated table of random numbers. Group assignments will be sealed in opaque envelopes to maintain blinding of the investigators, patients, and data analysts, and these envelopes will only be opened after the study is completed. The schedule of patient enrolment, study interventions, and outcome assessments will follow the SPIRIT statement (Table 1). All surgeries will be performed by experienced surgeons who have conducted at least 300 knee arthroplasty procedures prior to the study.

**TABLE 1 T1:** Schedule of patient enrolment, study interventions and outcome assessment.

Time point	Study period								
	Enrolment	Allocation	Post-allocation					Close-out	Follow-up
	Pre-op visit	Pre-op 1 day	Intraoperatively	PACU	24 h post-op	48 h post-op	72 h post-op	Discharged	3 months
Patient enrolment									
Eligibility criteria	×								
Written informed consent	×								
Demographic data	×								
Baseline characteristics	×								
HADS	×								
PCS	×								
Randomization/allocation		×							
Study interventions									
5% Lidocaine Patch		×			×	×	×		
Placebo Patch		×			×	×	×		
Outcome assessment									
WOMAC-Pain Scale	×								×
WOMAC-Stiffness Scale	×								×
WOMAC-Function Scale	×								×
WOMAC-Total Scale	×								×
LANSS									×
SF-36									×
Post-op pain scores					×	×	×		
VAS Sleep score					×	×	×		
Post-op sufentanil use							×		
Need for rescue analgesia							×		
Length of PACU stay				×					
Length of hospital stay								×	
90-day mortality									×
Adverse Events									
Hypotension			×	×	×	×	×		
Hypertension			×	×	×	×	×		
Bradycardia			×	×	×	×	×		
Tachycardia			×	×	×	×	×		
Arrhythmia			×	×	×	×	×		
HD Events Intervention			×	×	×	×	×		
Headache		×			×	×	×		
Dizziness		×			×	×	×		
Nausea and vomiting		×		×	×	×	×		
Local skin allergy		×			×	×	×		
Wound infection					×	×	×		
Toxic reaction		×			×	×	×		

According to SPIRIT, statement of defining standard protocol items for clinical trials.

HADS, hospital anxiety and depression scale; PCS, pain catastrophizing scale; WOMAC, Western Ontario and McMaster Universities Osteoarthritis Index; LANSS, leeds assessment of neuropathic symptoms and signs; SF-36, Short Form Health Survey; Pre-op, Preoperative; Post-op, Postoperative; VAS, visual analogue scale; PACU, post-anaesthesia care unit; HD, haemodynamic; h, hours; SPIRIT, Standard Protocol Items: Recommendations for Interventional Trials.

### 2.9 Anaesthetic care

Intraoperative monitoring will include non-invasive blood pressure (NIBP), electrocardiography (ECG), pulse oximetry (SpO_2_), radial artery blood pressure, and nasopharyngeal temperature. Anesthesia will be induced with an intravenous injection of propofol at 1.5–2.5 mg/kg, combined with sufentanil at 0.2–0.4 μg/kg for analgesia. This will be followed by an intravenous injection of rocuronium at 0.6–0.9 mg/kg to achieve muscle relaxation. After induction, an endotracheal tube will be inserted, and its placement will be confirmed. The patients will receive mechanical ventilation, maintaining end-tidal carbon dioxide between 35 and 45 mmHg. Hypotension (mean arterial pressure <65 mmHg or a decrease of 20% from baseline) and bradycardia (heart rate <50 beats/min) will be treated as needed. A thermal blanket will be used during the operation to maintain nasopharyngeal temperature above 36°C. Additional doses of rocuronium will be administered as necessary to maintain muscle relaxation throughout the procedure. Continuous monitoring will include ECG, NIBP, SpO_2_, and bispectral index (BIS), with BIS values maintained between 40 and 60. Both groups of patients received 50 mg of flurbiprofen axetil during surgery. Postoperatively, all patients were transferred to the PACU. During their stay in the PACU and hospitalization, if a patient reported pain with an NRS score of 4 or higher, 5 μg of sufentanil was administered for analgesia, and the total dosage was recorded.

### 2.11 Sample size calculation

Based on previous studies, the standard deviation (SD) of the WOMAC Pain Scale prior to surgery is approximately 17, which corresponds to an 8–9 unit difference on the scale, representing the minimum clinically perceptible improvement (Wylde et al., 2015). To detect a 0.5 SD difference in WOMAC Pain Scale scores at 3 months postoperatively, with a two-sided α = 0.05 and 80% power, a sample size of 57 patients per group is necessary. Considering a potential dropout rate of 10%, we plan to enroll a total of 128 patients, with 64 patients in each group.

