## 1 Introduction

As the population ages, the prevalence of knee osteoarthritis continues to rise, resulting in an increasing number of knee arthroplasty procedures (Nham et al., 2023). Although knee arthroplasty is a definitive treatment for this condition and offers significant benefits, chronic postsurgical pain (CPSP) remains a significant issue, affecting 10%–30% of patients undergoing the procedure (Beswick et al., 2012). CPSP not only diminishes the quality of life and surgical outcomes for patients but also escalates healthcare costs (Schug et al., 2019). Treating CPSP faces high failure rates, with systemic medications such as antidepressants and antiepileptics providing only limited efficacy and being associated with significant adverse effects (Steyaert and Lavand’homme, 2018).

The 5% lidocaine-medicated plaster (LP5) is a topical analgesic that provides pain relief and local anesthesia by inhibiting voltage-gated sodium channels in neurons (Baron et al., 2016). It has shown significant efficacy in treating postherpetic neuralgia and diabetic peripheral neuropathic pain (Pei-Lin et al., 2008; White et al., 2010). Research indicates that lidocaine in LP5 can penetrate the stratum corneum to reach peripheral nerve fiber endings, inhibiting the transmission of persistent nociceptive signals from peripheral nerves and reducing the sensitization and hyperexcitability of neurons in both the peripheral and central nervous systems (Maloney et al., 2021). Existing studies have shown that LP5 is an effective treatment for chronic localized neuropathic pain following knee surgery. Beginning on day 7 of use, 83% of patients (20/24) experienced a 50% reduction in dynamic mechanical allodynia within 3 months (Pickering et al., 2019). However, the effectiveness of LP5 in preventing CPSP following knee arthroplasty remains unclear. Most current research focuses on treating chronic pain, whereas our study emphasizes early intervention to prevent pain, particularly given the refractory nature of CPSP. This study aims to evaluate the efficacy of LP5 in preventing CPSP in patients undergoing knee arthroplasty. By thoroughly examining the impact of LP5 on CPSP, we aim to provide valuable insights and potentially establish a new standard for postoperative pain management, thereby improving patient outcomes.

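### The 0.5 SD target is called the minimum perceptible improvement on the strength of a pre-surgery SD, but the endpoint is the 3-month score, whose SD is not given

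*Protocol article*

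**What the plan says.** Section 2.11 (Sample size calculation) of the protocol article makes three linked statements.

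- The spread comes from before the operation: "the standard deviation (SD) of the WOMAC Pain Scale prior to surgery is approximately 17".
- That spread is given a clinical meaning: "which corresponds to an 8–9 unit difference on the scale, representing the minimum clinically perceptible improvement". The arithmetic behind this is 0.5 × 17 = 8.5.
- The trial is then sized at another time point: "To detect a 0.5 SD difference in WOMAC Pain Scale scores at 3 months postoperatively", "with a two-sided α = 0.05 and 80% power", for which "a sample size of 57 patients per group is necessary". After a 10% dropout allowance, "we plan to enroll a total of 128 patients, with 64 patients in each group".

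Sections 2.4 and 2.12 confirm that the primary endpoint is the 3-month WOMAC pain score, analysed by linear regression with adjustment for baseline WOMAC pain, HADS, PCS, sex, age and BMI. The article gives neither an SD for the 3-month score nor a correlation between baseline and 3-month scores.

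**The concern.** The claim of clinical relevance lies in the step from SD units to scale units, and that step uses the SD from the wrong time point. Before surgery every participant is awaiting a knee replacement. After surgery the Introduction expects chronic pain "affecting 10%–30% of patients undergoing the procedure", so the 3-month sample mixes a minority with persistent pain and a majority without. The article gives no reason why the two spreads should be equal.

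What is at stake is the reading of a null result. A reader of section 2.11 could take it that a perceptible difference would have been detected with 80% power. If the 3-month SD is larger than 17, power for 8–9 units is lower than that reader assumes. If it is smaller, half an SD is less than the plan's own minimum, and the label put on the target is wrong.

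**Working it through.** **Inputs.** From section 2.11: pre-surgery SD 17; minimum 8–9 units; target 0.5 SD; two-sided α 0.05; power 80%; 57 per arm before dropout; 64 per arm enrolled. From section 2.12: covariate-adjusted regression. Assumed, because the article does not give them: 3-month SDs of 14 to 20, and baseline to 3-month correlations r of 0.3 and 0.5.

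**Step 1: the plan's own figure.** Normal approximation: n per arm = 2 × [(1.960 + 0.842) × SD / difference]².

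- Difference 8.5, SD 17 (exactly 0.5 SD): 2 × (2.802 × 2)² ≈ 62.8, so 63. The two-sample t-test needs 64.
- Difference 9, SD 17 (0.53 SD): 56.01, so 57. The t-test also gives 57.
- Difference 8, SD 17: 70.9, so 71. The t-test gives 72.

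The stated 57 is therefore not reproduced for 0.5 SD; it fits only a difference of 9 units with SD 17. The dropout step is correct: 57 / 0.9 = 63.3, so 64.

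**Step 2: power at the plan's own SD.** With SD 17 and 57 per arm, the standard error of the difference is 17 × √(2/57) = 3.18. Unadjusted t-test power is 70% for 8 units, 75% for 8.5 and 80% for 9. The gap between 75% and 80% has nothing to do with timing; it is the shortfall from Step 1.

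**Step 3: other 3-month SDs.** Unadjusted t-test, 57 per arm:

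| Assumed 3-month SD | Half an SD (units) | Power for 8 | Power for 8.5 | Power for 9 |
|---|---|---|---|---|
| 14 | 7 | 86% | 90% | 93% |
| 17 | 8.5 | 70% | 75% | 80% |
| 20 | 10 | 56% | 61% | 66% |

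Power for a standardised 0.5 SD is 75% in every row. Only the power for a difference fixed in units moves. By the normal approximation, 80% power for 8.5 units with 57 per arm requires an SD of no more than 8.5 / [2.802 × √(2/57)] = 16.2.

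**Step 4: baseline adjustment.** Residual SD = SD × √(1 − r²). Power for 8.5 units, 57 per arm:

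- SD 17, r = 0.3: residual SD 16.2, power 79%.
- SD 17, r = 0.5: residual SD 14.7, power 86%.
- SD 20, r = 0.5: residual SD 17.3, power 74%.

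**The case against.** The strongest reply is that the 80% is attached to a standardised difference. Power for 0.5 SD does not depend on the SD at 3 months, so an unknown 3-month SD cannot by itself make the 80% wrong. That stands. A reader might infer that use of the pre-surgery SD invalidates the stated power, or that the trial is underpowered because of it; the article supports neither. What remains is that section 2.11 justifies 0.5 SD by equating it with 8–9 units, and that equation is not supported at 3 months.

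Second, the range of SDs is assumed. This is also true. The article fixes neither the size nor the direction of any departure from 17, and the cited source of the 17 is not at hand, so it cannot be said whether that source supports a similar postoperative SD.

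Third, the planned regression works with the residual SD, so unadjusted figures understate power. This stands too, but section 2.11 neither invokes adjustment nor states a correlation, and at SD 20 even r = 0.5 leaves power below 80%.

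A reader might also infer that a significant result would wrongly be taken as proof of a perceptible benefit. That does not follow from the timing of the SD. At SD 17 with 57 per arm, an observed unadjusted difference of about 6.3 units (1.98 × 3.18) is already significant, so the caution would apply even with a perfectly known 3-month SD. The article does not say that it will read results in that way.

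**Conclusion.** The point holds in a limited form. Section 2.11 calls its target the minimum perceptible improvement by means of an SD from a different time point than the endpoint, and no 3-month SD is given to support this. Power for 8–9 units at 3 months is therefore not established, and it cannot be told from the article whether it is better or worse than a reader would assume.

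The size is conditional: about 90% to 61% for 8.5 units over assumed SDs of 14 to 20, unadjusted, with 57 evaluable per arm, and higher with adjustment by an unknown amount. The 75% at SD 17 should be credited to the choice of 57 rather than 64 for 0.5 SD, not to the time-point mismatch. Which scale the 17 and the 8–9 units refer to, given the 0–50 range in section 2.4, is a separate question; the mismatch in timing remains whatever the answer.

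**What to change.** In section 2.11:

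- State the target as a difference in units at 3 months, on the scale actually used.
- Replace the single 80% by power for that difference over a stated range of 3-month residual SDs. Include the correct figure at SD 17 (about 75% unadjusted for 8.5 units with 57 per arm) and state any correlation assumed for the adjustment.
- Do not call 0.5 SD the minimum perceptible difference unless a 3-month SD is cited that supports it.
- Say that a null result will be judged by the confidence interval for the adjusted difference, in units, against 8–9.

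This costs a few sentences and a short table. Enrolment, endpoint and primary analysis stay as they are. The downside is that the stated power may look less favourable than a single 80%.

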### 2.7 Randomization and blinding

An independent researcher will generate random numbers using an online tool (https://www.sealedenvelope.com/simple-randomiser/v1/lists) with a 1:1 allocation ratio, stratified by center. Randomization results will be stored in sealed opaque envelopes. Patients will be assigned to either the LP5 group or the placebo group. Postoperative care providers will prepare 5% lidocaine and placebo patches with patient numbers marked on the outer packaging. Patients, surgeons, anesthesia providers, outcome assessors, and statisticians will be blinded to group allocation.

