### 2.12 Statistical analysis

The normality of continuous variables will be assessed via the Shapiro-Wilk test. Normally distributed data will be presented as mean (standard deviation), whereas non-normally distributed data will be presented as median (interquartile range). For normally distributed continuous variables, independent t-tests or repeated measures ANOVA will be utilized for analysis. For non-normally distributed variables, the Mann-Whitney U test or generalized estimating equations (GEE) will be employed. Categorical data will be expressed as numbers (percentages) and analyzed via the chi-square test or Fisher’s exact test, depending on the expected frequencies. The primary outcome, the WOMAC-pain score at 3 months postoperatively, will be analyzed via a linear regression model, adjusting for baseline variables including HADS scores, PCS scores, baseline WOMAC-pain scores, sex, age, and BMI. Additionally, interactions between the treatment group and baseline scores of HADS, PCS, and WOMAC-pain will also be examined. Covariates with *p*-values <0.10 will be retained in the final model. Secondary outcomes will undergo multiple testing corrections via the Benjamini–Hochberg method, with the false discovery rate (FDR) significance level set at q < 0.05. Odds ratios (OR) and 95% confidence intervals (CI) will be reported where applicable. To ensure the robustness of our primary findings, we will conduct a sensitivity analysis using the bootstrap method. The bootstrap analysis will involve 1,000 resamples to estimate the regression coefficients and their 95% confidence intervals (CIs). This analysis will provide additional validation for the stability of the initial regression results. All results will be analyzed using a modified intention-to-treat approach, including all patients who undergo randomization and for whom relevant data are available. Statistical analyses will be conducted via SPSS software (version 25.0; IBM SPSS). A two-sided *p*-value <0.05 will be considered statistically significant unless specified otherwise for false discovery rate (FDR) corrections. Missing data will not be imputed, and no interim analyses are planned.

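### 57 patients per group does not give 80% power for a 0.5 SD difference: 64 are needed, and after the planned 10% dropout an unadjusted comparison has about 75% power

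*Protocol article*

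**What the plan says.** All the inputs are in section 2.11 of the protocol article, except the allocation ratio.

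- **SD:** "the standard deviation (SD) of the WOMAC Pain Scale prior to surgery is approximately 17".
- **Clinical benchmark:** the section continues "which corresponds to an 8–9 unit difference on the scale, representing the minimum clinically perceptible improvement".
- **Target:** "To detect a 0.5 SD difference in WOMAC Pain Scale scores at 3 months postoperatively".
- **Error rates and result:** "with a two-sided α = 0.05 and 80% power, a sample size of 57 patients per group is necessary".
- **Dropout:** "Considering a potential dropout rate of 10%, we plan to enroll a total of 128 patients, with 64 patients in each group".
- **Allocation (section 2.7):** "with a 1:1 allocation ratio, stratified by center".

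Section 2.12 says the primary outcome "will be analyzed via a linear regression model, adjusting for baseline variables including HADS scores, PCS scores, baseline WOMAC-pain scores, sex, age, and BMI". It also says that missing data are not imputed and that only patients with relevant data are analysed. Section 2.11 mentions no covariate adjustment, correlation or R².

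**The concern.** A standardised difference of 0.5 at two-sided 5% and 80% power is a textbook case, and its answer is 63 or 64 per group. The protocol gives 57 before the dropout allowance and reaches 64 only after adding it. The margin meant to cover losses is therefore already needed to reach 80% power with complete data.

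This statement justifies the trial's size for its primary outcome, and a null result at 3 months would be read against it. If power at 0.5 SD is nearer 75%, such a result says less about the absence of a 0.5 SD effect than the protocol claims. At the lower end of the range the protocol calls minimally perceptible, the gap is wider.

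**Working it through.** **Inputs.** Difference 0.5 SD (8.5 units at SD 17), two-sided α = 0.05, power 80%, 10% dropout (section 2.11); 1:1 allocation (section 2.7).

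**1. Required size from the stated inputs.** Normal approximation, per group:

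n = 2(z₀.₉₇₅ + z₀.₈₀)² / d² = 2(1.960 + 0.842)² / 0.5² = 62.8, so 63.

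The noncentral-t calculation gives 63.77, so 64. The stated 57 is not reproduced by either method.

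**2. Where 57 could come from.** Unadjusted t-test, 80% power:

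| Difference | d | Test | n per group |
|---|---|---|---|
| 8 units | 8/17 = 0.471 | two-sided | 71.9 |
| 8.5 units | 0.500 | two-sided | 63.8 |
| 9 units | 9/17 = 0.529 | two-sided | 56.98 |
| 8.5 units | 0.500 | one-sided | 50.2 |
| 8 units | 0.471 | one-sided | 56.5 |

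Of the two-sided calculations, only the 9-unit difference gives 57. A one-sided test at 0.5 SD does not. A one-sided test at 8 units also rounds up to 57, but the protocol specifies a two-sided test. At 0.5 SD, two-sided, 56.5 per group is the size for 75% power. The likeliest explanation is that 9 units was used and described as 0.5 SD. That is an inference; the mismatch between 57 and 0.5 SD is not.

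**3. Power actually obtained** (t-test, two-sided 5%):

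| Evaluable per group | 8 units (0.471 SD) | 0.5 SD | 9 units (0.529 SD) |
|---|---|---|---|
| 57 | 70.2% | 75.4% | 80.0% |
| 57.6 (= 64 × 0.9) | 70.7% | 75.8% | 80.4% |
| 64 (no losses) | 75.2% | 80.1% | 84.4% |

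By the normal approximation, power at 57 per group and 0.5 SD is 76.1%, so the choice of method does not explain the gap.

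**4. Dropout step.** 57/0.9 = 63.3, so 64: correct arithmetic on the wrong starting number. From 64 evaluable, 64/0.9 = 71.1, so 72 per group (144 in total). From 63, 63/0.9 = 70 per group (140 in total).

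**5. Effect of covariate adjustment.** If the covariates together correlate at r with the 3-month score, the residual variance is multiplied by (1 − r²). Setting 63.77(1 − r²) = 57 gives r² = 0.106, so r ≈ 0.33. Power at 57 per group and 0.5 SD, with r as an assumption:

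| r | 0.1 | 0.2 | 0.3 | 0.4 | 0.5 |
|---|---|---|---|---|---|
| Power | 75.8% | 77.1% | 79.2% | 82.3% | 86.3% |

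**The case against.** The strongest reply is that the primary analysis is not a two-sample t-test. Section 2.12 adjusts for baseline WOMAC pain, HADS, PCS, sex, age and BMI, and step 5 shows that a correlation of about 0.33 is enough to reach 80% at 0.5 SD with 57 per group. True power could therefore lie on either side of 80%, and the 75% describes only an unadjusted comparison. That qualification stands. It does not make the stated calculation right, because section 2.11 uses no adjustment and gives no correlation, and the protocol offers no figure from which one could be taken.

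A second reply is that this is loose labelling: N follows from 9 units, which the section quotes, and the shortfall is only about 5 percentage points. This is plausible, and the size is indeed modest. But 9 units is the favourable end of an 8–9 unit range, and at 8 units the same N gives 70%. The estimate, its confidence interval and the type I error are unaffected; the fault is confined to the design claim.

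A third point concerns units. Section 2.4 puts the outcome on a 0–50 scale, and section 2.11 does not say which scale its SD of 17 and its 8–9 units belong to. The SD is also a preoperative one. The standardised result at 0.5 SD does not depend on this, but any statement in raw units does.

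**Conclusion.** The sample size statement is wrong as written. For 0.5 SD, two-sided 5% and 80% power, 64 evaluable patients per group are needed (63 by the normal approximation), not 57. With the 57 to 58 per group expected after 10% dropout, an unadjusted comparison has 75–76% power at 0.5 SD. The difference detectable with 80% power at 57 per group is 0.529 SD, or 9.0 units if the SD is 17.

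These figures assume equal groups, a common SD, the dropout the protocol itself expects, and no gain from covariates. The adjusted model reaches 80% at 0.5 SD if the covariates correlate with the 3-month score at about 0.33 or more, which the protocol does not claim. The shortfall is modest, but it lies in the justification for the primary outcome and nothing else in the document corrects it.

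**What to change.** Keep N = 128 and correct section 2.11 in one of two ways.

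- **(a) State what the design delivers.** 57 evaluable patients per group give 80% power (two-sided 5%, unadjusted) for 0.53 SD, which is 9 units at SD 17, and 75% for 0.5 SD. Add that power is 70% at 8 units, since the section names 8–9 units as the perceptible range. Confirm first which scale the SD and the units refer to.
- **(b) Base the calculation on the adjusted model in section 2.12.** Name the covariates relied on, state the assumed correlation with the 3-month score and its source, and show power across 0.2 to 0.5 (77% to 86% at 57 per group and 0.5 SD). The threshold of 0.33 is only what would be required, not evidence that it will be met.

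Either way the cost is a rewording of one section, with no extra patients. Under (a) the stated power or detectable difference becomes slightly less favourable; under (b) the 80% claim rests on a stated assumption. For comparison, keeping 0.5 SD, 80% power and 10% dropout without adjustment would take 72 per group, 16 more patients in total (144 − 128).
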